## Abstract

**Objective:**

Ultra‐high dose rate FLASH radiotherapy (FLASH‐RT) is emerging as a novel technique to improve the normal tissue tolerance by delivering ultra‐high dose rate radiation several orders of magnitude higher than convention radiotherapy. It has been shown in preclinical studies to cause less injury to surrounding normal tissues during radiation treatment, while still maintaining local tumor control. The purpose of this protocol is to evaluate the safety of fractionated FLASH‐RT in skin cancer.

**Method:**

Patients with superficial skin tumors will be enrolled. The eligible patients will undergo electron FLASH‐RT (24‐40 Gy/3‐5 fractions) to the tumor volume. The primary outcome is to evaluate the safety of FLASH‐RT by collecting the acute (< 90 days) skin toxicity adverse events of radiation according to Common Terminology Criteria for Adverse Events (CTCAE) version 5.0. Secondary objectives include late (> 90 days) skin toxicity after FLASH‐RT according to CTCAE version 5.0 and treatment response.

**Discussion:**

If the results show that delivering FLASH‐RT is safe and feasible for skin tumors, further investigation will be conduct to evaluate efficacy of FLASH‐RT in a phase II trial.

**Trial Registration number:**

ChiCTR2400080935. https://www.chictr.org.cn/showproj.html?proj=220336

## INTRODUCTION

1

Skin cancer is one of the most common cancer across the world, squamous cell carcinoma and basal cell carcinoma are the two major types of nonmelanoma skin cancer.^1^ Radiotherapy is an important component for the management of nonmelanoma skin cancer, both in the definitive and palliative setting.^2^

Over the last 30 years, conventional radiotherapy is delivered in fractions to maximize the destruction of malignant cells while minimizing damage to healthy tissues. Technological innovations in radiation oncology led to the development of precision radiotherapy, and the capability of accurately and safely delivering complex‐shaped dose distributions has been improved in conventional radiotherapy.^3^ Unfortunately, the overall clinical response rate of radiotherapy remains poor. Escalation of radiation doses to cancer cells is a promising method to sterilize any tumor and achieve nearly 100% of tumor control. However, the surrounding healthy tissue damage is a key challenge for the delivery of high dose of radiation.^4^

FLASH‐RT is radiation treatment delivered at ultra‐high dose rates (mean dose rate ≥ 40 Gy/s) compared to conventional radiation treatment (usually ≤ 10 Gy/min).^5^ The radiation dose can be delivered almost instantaneously in milliseconds after FLASH‐RT, and this dose rate are believed to cause less damage to normal tissue, also called as FLASH effect.^6^

In recent years, the FLASH effect has been reported in various animal models with different types of irradiations including electron, photon, and proton.^6^, ^7^, ^8^ Although the mechanism of FLASH‐RT in alleviating normal tissue damage is still under investigation, oxygen depletion, peroxyl radical recombination, and immune cell protection are supposed to be essential for the FLASH effect.^5^ This dramatic increase of the differential effect between tumors and normal tissues accelerated its clinical translation. In 2019, Lausanne University Hospital (CHUV) performed electron FLASH‐RT in a patient combined with multi‐resistant CD30+ T‐cell cutaneous lymphoma, there was favorable outcome in this case both on normal skin and the tumor; the results indicated electron FLASH‐RT is feasible and safe.^9^, ^10^ Furthermore, Cincinnati Children's Hospital Medical Center reported the feasibility and safety of proton FLASH‐RT in patients with extremity bone metastases in FAST‐01 clinical trial.^11^ These findings supported the further evaluation of FLASH‐RT in patients with cancer.

The aim of this Phase I study (ChiCTR2400080935) was designed to describe and evaluate the toxicity and efficacy of FLASH‐RT in patients presenting localized superficial skin tumor requiring a radiation treatment.

## METHODS

2

### Objectives

2.1

The primary objective of this study is to evaluate the safety and acute radiation‐related toxicity (≤ 90 days) in patients with localized superficial skin tumor after FLASH‐RT using National Cancer Institute (NCI) Common Terminology Criteria for Adverse Events (CTCAE v5.0).^12^

The secondary objectives are as follows: 1. To evaluate late toxicity (> 90 days) of FLASH‐RT in patients with localized superficial skin tumor from time of radiation. 2. Estimate treatment efficacy of FLASH‐RT with the Response Evaluation Criteria in Solid Tumors (RECIST) criteria (v1.1) after radiotherapy.^13^

### Study design

2.2

This is a single institution, prospective, single arm safety study to evaluate the feasibility and safety of electron FLASH‐RT in patients with localized superficial skin tumor. Patients with localized superficial skin tumor will be considered for enrolling in this phase I study. All the eligible patients will be discussed at multi‐disciplinary meeting. Patients will be formally recruited and managed by members of the FLASH‐RT team. The treatment protocol is shown in Figure 1.

**FIGURE 1 pro670010-fig-0001:**
[figure not shown]
Study protocol schema. FLASH‐RT, Ultra‐high dose rate FLASH radiotherapy.

### Interventions (FLASH‐RT)

2.3

The radiation plan for eligible patients are as following: For T1 (small) lesions: 3×8 Gy fractionated dose FLASH‐RT; For T2 (large) lesions: 5×8 Gy fractionated dose FLASH‐RT. FLASH‐RT will be delivered to all patients using 9 MeV electrons. The parameters were as following: source skin distance, 100 cm; instantaneous dose rate, 82500 Gy/s; average dose rate, 120 Gy/s; pulse width, 4.0 µs; frequency, 360 Hz; pulse number, 360. Detail of the linear accelerator used for FLASH‐RT were reported previously (supplementary Figure 1).^14^ All the parameters were measured and certificated by China Institute of Atomic Energy. Dosimetric checks were conducted before, after and during FLASH‐RT. The dose distribution of FLASH‐RT will be measured by both alanine pelets and Gafchromic HD‐V2 Film.

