### Rational for radiation dose

2.4

The total radiation doses delivered for tumors were: 24 Gy in 3 fractions (biologically effective dose (BED_10_) = 43.2 Gy) for T1 disease, and 40 Gy in 5 fractions (BED_10_ = 72.0 Gy) for T2 disease. This dose was applied because BED_10_ between 40 and 72 has been associated with excellent overall cure rates for superficial skin tumor.^2^

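### The pulse number in section 2.3, taken with the other listed beam parameters, implies about 119 Gy and cannot be reconciled with the 8 Gy fraction or with either full course

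*Protocol article*

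**What the plan says.** Section 2.3 (Interventions) sets the prescription by lesion size: "For T1 (small) lesions: 3×8 Gy fractionated dose FLASH‐RT" and "For T2 (large) lesions: 5×8 Gy fractionated dose FLASH‐RT". Section 2.4 (rationale for dose) repeats it as totals, "24 Gy in 3 fractions" for T1 and 40 Gy in 5 fractions for T2, with BED10 values of 43.2 and 72.0 Gy.

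Section 2.3 then moves to the beam: "FLASH‐RT will be delivered to all patients using 9 MeV electrons. The parameters were as following". The list that follows includes "instantaneous dose rate, 82500 Gy/s; average dose rate, 120 Gy/s", a pulse width of 4.0 µs, and "frequency, 360 Hz; pulse number, 360". The section adds that an outside institute measured and certified the parameters, and that dosimetric checks accompany treatment. It gives no other pulse number and does not say whether 360 is the count per fraction, per course, per second or for a measurement run.

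**The concern.** The parameter list comes directly after the statement that all patients will be treated with 9 MeV electrons, so a reader takes it as the treatment specification. In-pulse dose rate, pulse width and pulse count together fix a dose. That dose should match 8 Gy if the count refers to a fraction, or 24 or 40 Gy if it refers to a course. It matches none of them.

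This is a single-arm phase I study whose primary objective is safety and acute radiation toxicity (sections 2.1 and 2.2). The delivered exposure is the experimental variable. A later reader who wants to interpret the toxicity results, or to reproduce the delivery in the phase II trial that the abstract foresees, needs a specification whose figures agree. The contradiction lies between printed values, so it is not a matter of detail that an article leaves to a fuller document.

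**Working it through.** **Inputs** (section 2.3 unless noted): in-pulse dose rate 82500 Gy/s; pulse width 4.0 µs; frequency 360 Hz; pulse number 360; stated average dose rate 120 Gy/s; fraction dose 8 Gy; course doses 24 Gy and 40 Gy (section 2.4); FLASH threshold, mean dose rate at least 40 Gy/s (Introduction).

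**Step 1: reproduce the plan's own average dose rate.**
- Dose per pulse = in-pulse rate × width = 82500 × 4.0×10⁻⁶ = 0.33 Gy.
- Average rate = dose per pulse × frequency = 0.33 × 360 = 118.8 Gy/s.
- The stated value is 120 Gy/s, a difference of 1%. These four parameters agree, so the formula and units have been read correctly.

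**Step 2: reproduce the prescription.** BED10 = n × d × (1 + d/10).
- T1: 3 × 8 × 1.8 = 43.2 Gy, as stated.
- T2: 5 × 8 × 1.8 = 72.0 Gy, as stated.

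The 8 Gy fraction is therefore consistent within sections 2.3 and 2.4.

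**Step 3: bring in the pulse number.**
- Exposure time = 360 / 360 Hz = 1.0 s.
- Implied dose = 360 × 0.33 = 118.8 Gy (120 Gy if the stated average rate is used).

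| Reading of the 360 pulses | Prescribed dose | Implied / prescribed |
|---|---|---|
| One fraction | 8 Gy | 118.8 / 8 = 14.85 |
| Whole T1 course | 24 Gy | 118.8 / 24 = 4.95 |
| Whole T2 course | 40 Gy | 118.8 / 40 = 2.97 |

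**Step 4: can rounding explain it?** Assume that the in-pulse rate could lie between 81500 and 83500 Gy/s and the width between 3.95 and 4.05 µs. These ranges are assumptions, not figures from the article.
- Low: 81500 × 3.95×10⁻⁶ × 360 = 115.9 Gy, 14.5 times 8 Gy.
- High: 83500 × 4.05×10⁻⁶ × 360 = 121.7 Gy, 15.2 times 8 Gy.

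Rounding does not close the gap.

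**Step 5: the converse.** Suppose 360 pulses did deliver 8 Gy.
- Dose per pulse = 8 / 360 = 0.0222 Gy.
- In-pulse rate = 0.0222 / 4.0×10⁻⁶ ≈ 5556 Gy/s, against 82500 stated.
- Average rate = 0.0222 × 360 = 8 Gy/s, against 120 stated and the threshold of 40.

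**For comparison only:** at 0.33 Gy per pulse, 8 Gy corresponds to 8 / 0.33 ≈ 24.2 pulses, or about 67 ms at 360 Hz. This is arithmetic on the printed values, not a proposed setting.

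**The case against.** The best defence is that the article never attaches the 360 pulses to a fraction. The list is in the past tense and is followed by a statement about outside measurement and certification. At 360 Hz, 360 pulses make exactly one second, and 120 Gy/s over one second is 120 Gy. The listed values therefore fit together as a characterisation run, or 360 may simply be the pulses per second written twice. Accelerator details are referred to a cited report and a supplementary figure, neither of which is shown, and either could define the number. This stands, and it is why the point is framed as an unreconciled figure and not as a delivered dose. It does not remove the problem, because the text places the number among the parameters for treating all patients and gives no other meaning.

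Two stronger readings are tempting.

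- A reader might infer that patients would receive about 119 Gy. The documents do not support that. The prescription is stated consistently, the BED10 values reproduce from 8 Gy, and section 2.3 describes dosimetric checks before, during and after treatment, with alanine and film measurement. Nothing indicates that the article is used to set the machine.
- A reader might infer from step 5 that the treatment falls below the article's own FLASH threshold. That would require the in-pulse and average dose rates both to be wrong by about 15-fold and in step, although they agree with each other within 1%.

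The Introduction's remark that "The radiation dose can be delivered almost instantaneously in milliseconds" is general background. It sits more easily with about 67 ms than with a full second, but it does not specify this trial's delivery and carries no weight here.

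**Conclusion.** The point holds as an internal contradiction in the intervention specification. In-pulse rate, width, frequency and average rate agree with one another, and the fraction dose, course dose and BED10 agree with one another. The pulse number does not connect the two sets: it implies about 119 Gy in 1 s, roughly 15 times the fraction and about 5 and 3 times the full courses. The conclusion assumes that dose is in-pulse rate × width × number of pulses, which the agreement in step 1 supports, and that the listed values describe patient treatment, as their position in section 2.3 suggests.

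The likeliest explanations are a reporting error in the pulse number or an unlabelled characterisation setting, and the article does not allow a choice between them. It supports neither a conclusion that patients would be overdosed nor one that the beam is not FLASH. The point still needs correction, because exposure is the variable under test in a safety study.

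**What to change.** The sponsor's physicists should reconcile the pulse number in section 2.3 with the 8 Gy fraction in sections 2.3 and 2.4 and with the other stated beam parameters, using the certified measurements. They should then either correct the figure or label separately which settings belong to beam characterisation and which to a patient fraction. Which figure is right is for them to establish; no dose or machine setting is proposed here.

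The cost is a check against a certificate that section 2.3 says exists, and a short correction of the text. Sample size, endpoints and timelines are unaffected.

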### Rational for radiation dose

2.4

The total radiation doses delivered for tumors were: 24 Gy in 3 fractions (biologically effective dose (BED_10_) = 43.2 Gy) for T1 disease, and 40 Gy in 5 fractions (BED_10_ = 72.0 Gy) for T2 disease. This dose was applied because BED_10_ between 40 and 72 has been associated with excellent overall cure rates for superficial skin tumor.^2^

### Follow‐up

2.5

Radiation‐induced adverse events will be assessed according to NCI‐CTCAE (v5.0).^12^ Acute toxicity will be monitored and recorded on a weekly basis during the first 3 months. Late toxicity will be evaluated and recorded thereafter. Treatment response will be assessed by using the RECIST criteria (v1.1).^13^ Patient follow‐up is typically scheduled in clinic every 3 months for the first 2 years post‐FLASH‐RT and every 6 months thereafter by performing physical examination, computed tomography imaging, and routine laboratory test.

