### Inclusion criteria

2.6

Patients must fulfill all the following criteria to be eligible for inclusion in this study:

(1) Age: 18–75 years old. (2) Patients with histologically proven cutaneous squamous cell carcinoma or basal cell carcinoma. (3) Without distant metastasis. (4) Without any other medical condition or laboratory value that would, at the discretion of the investigator, preclude the patient from participation in this clinical investigation. (5) Without any serious underlying medical condition that could interfere with study treatment and potential adverse events. (6) The Eastern Cooperative Oncology Group (ECOG) score: 0–2. (7) Patients requiring radiotherapy treatment according to the dermato‐oncology tumor board: standard treatment is ineffective, patients who are either medically inoperable or refuse to surgical resection, and/or anatomical locations where surgery can compromise function or cosmesis. (8) The disease progression affects patients’ quality of life. (9) T1‐T2 N0 lesions with a small (T1; lesion ≤ 2cm in diameter) or large (T2; 2cm < lesion ≤ 4 cm) volume (the Union for International Cancer Control (UICC) Classification of Malignant Tumours, 8th Edition); the size of the treated lesion should be ≤ 3.5 cm thick (caliper‐based measurement). (10) Clinically acceptable treatment plan with electron FLASH‐RT. (11) Treatment associated side effects are limited and controllable. (12) Life expectancy ≥ 3 months (in the judgement of the investigator). (13) A FLASH‐RT team consisting of 4 radiation oncologists, 3 radiation physicists, and 1 dermatologist should be established prior to radiotherapy. (14) No antibiotics, hormones, immunosuppressive drugs, probiotics, etc. were used within 1 month prior to treatment. (15) Patients who can comply with the protocol. (16) Sign the phase I study informed consent form.

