### Safety stopping rules

2.9

FLASH‐RT will be delayed until toxicity improves to less than grade 2 in case any of the following adverse events: White blood cell count < 1.5 × 10^9^ cells/L; Absolute neutrophil count < 1.0 × 10^9^ cells/L; Platelets < 40 × 10^9^ cells/L; ≥ grade 3 non‐hematological toxicity.

If skin infection is observed in the tumor area with fever over 38.5°C, FLASH‐RT will be delayed until complete recovery. And FLASH‐RT will be terminated if the patient does not recover within 2 weeks.

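### The primary acute-toxicity outcome admits only events judged radiation-related, so in 12 uncontrolled patients with tumour in the treated skin the reported rate rests on a causality judgement that cannot be checked

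*Protocol article*

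**What the plan says.** The restriction by cause appears in three places in the protocol article.

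- **Abstract, Method:** safety is to be evaluated by "collecting the acute (< 90 days) skin toxicity adverse events of radiation according to Common Terminology Criteria for Adverse Events (CTCAE) version 5.0".
- **Section 2.1, Objectives:** the primary objective is to "evaluate the safety and acute radiation‐related toxicity (≤ 90 days) in patients with localized superficial skin tumor".
- **Section 2.5, Follow-up:** "Radiation‐induced adverse events will be assessed according to NCI‐CTCAE (v5.0".

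On design, section 2.2 states: "This is a single institution, prospective, single arm safety study". Section 2.6 (items 2 and 8) admits patients with proven squamous or basal cell carcinoma of the skin whose disease progression already affects quality of life. Section 2.8 gives 12 patients and descriptive statistics. The abstract's Discussion says that a finding of safety and feasibility would lead on to a phase II trial.

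**The concern.** An event enters the primary count only after someone has decided that radiation caused it. Three features make that decision hard to trust here.

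First, the treated site is diseased. A skin carcinoma can ulcerate, bleed, hurt or become infected, and severe acute skin toxicity can take the same forms. Attribution is least certain for the events that matter most.

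Second, there is no comparator. In a randomised trial, misattribution would tend to affect both arms and could be judged against the control rate. Here nothing can correct it.

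Third, human experience with the modality is thin by the article's own account. The completed cases in its section 3 are one lymphoma patient given a single 15 Gy electron dose and ten bone-metastasis patients given a single 8 Gy proton dose. This trial uses several 8 Gy fractions. Deciding what counts as radiation-related presupposes part of what the trial is meant to find out.

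At stake is the rate on which the safety conclusion, and so the step to phase II, would mainly rest.

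**Working it through.** **1. Is the restriction stated, or only inferred?** It is stated. The abstract, section 2.1 and section 2.5 each attach a causal qualifier to the events. No section says that acute events enter the primary outcome regardless of cause. Section 2.1 also names safety, which is a wider word, but the abstract specifies how safety is to be measured, and it does so by events of radiation.

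**2. The plan's own figure.** The only one is the sample size, n = 12 (section 2.8). It comes with no target rate, precision, alpha or power, so it cannot be reproduced. The calculations below use n = 12 as given.

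**3. Weight of one attribution.** 1/12 = 8.3 percentage points per patient.

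**4. Effect on the interval.** Exact (Clopper-Pearson) two-sided 95% limits at n = 12:

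- 0/12: upper limit = 1 − 0.025^(1/12) = 26.5%.
- 1/12: the upper limit is the p that solves (1 − p)^12 + 12p(1 − p)^11 = 0.025, which gives 38.5%; the lower limit is 0.2%.
- 2/12 = 16.7%: 2.1% to 48.4%.

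If one patient has a severe in-field event and it is put down to the tumour, the report changes from 8.3% (0.2% to 38.5%) to 0% (0% to 26.5%). If two are re-attributed, it changes from 16.7% (2.1% to 48.4%) to the same 0%.

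**5. Chance of reporting no severe event.** Let p be the true proportion of patients with a severe acute in-field event, and m the share of those patients whose event is attributed elsewhere. Then P(none reported) = (1 − p(1 − m))^12. The documents give neither p nor m, so both are assumptions, shown over a range:

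| True rate p | All counted (m = 0) | m = 25% | m = 50% |
|---|---|---|---|
| 10% | 0.90^12 = 28.2% | 0.925^12 = 39.2% | 0.95^12 = 54.0% |
| 20% | 0.80^12 = 6.9% | 0.85^12 = 14.2% | 0.90^12 = 28.2% |
| 30% | 0.70^12 = 1.4% | 0.775^12 = 4.7% | 0.85^12 = 14.2% |

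At an assumed true rate of 20%, attributing half of the events elsewhere raises the chance of a clean report about fourfold (28.2/6.9 = 4.1).

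**The case against.** Treatment-related toxicity is a recognised safety endpoint, and counting everything in the field has its own fault: ulceration from the tumour, or breakdown of a responding tumour, would count as toxicity with no control arm to separate it. The article is also a condensed account, and the full protocol may describe how cause is assigned. The plan sets no numerical safety threshold, so no stated decision flips, and the intervals for 0/12 and 1/12 overlap heavily. All of this is fair, and it limits the size of the point. It does not remove it. An attribution procedure would sit on top of the stated endpoint without lifting its restriction, and the trade-off between the two definitions is best handled by reporting both.

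Four stronger readings are tempting, and the article does not support them.

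- **The treating team filters its own results.** Section 2.2 says "Patients will be formally recruited and managed by members of the FLASH‐RT team". That covers recruitment and management; it does not say who judges cause.
- **In-field infection is excluded from toxicity.** Section 2.9 says "If skin infection is observed in the tumor area with fever over 38.5°C, FLASH‐RT will be delayed until complete recovery". That rule governs the timing of treatment. It neither includes infection in the outcome nor excludes it.
- **Events judged unrelated go unrecorded.** Section 2.5 also provides for weekly recording of acute toxicity without a causal qualifier, and the grade 3 trigger in section 2.9 has none either. Such events may well be recorded. The concern is what enters the primary count.
- **Pre-existing ulceration will be counted as toxicity.** The article describes no pre-treatment grading of the lesion, but a condensed article may leave that to the full protocol. A causal restriction would in any case tend to keep such findings out.

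**Conclusion.** The point holds as a weakness in the stated outcome definition. The primary acute-toxicity result is restricted to events judged radiation-related, in a single-arm trial of 12 patients whose treated skin carries a carcinoma, so the reported rate depends on a judgement that the design cannot test. Each re-attributed patient moves the rate by 8.3 points, and one is enough to lower the exact upper limit from 38.5% to 26.5%.

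Those figures need only n = 12. The probabilities of a clean report rest on assumed true rates of 10% to 30% and assumed re-attribution shares of 25% to 50%; they illustrate the sensitivity and do not predict that events will be misattributed. The conclusion does not depend on who assigns cause, on how infection is classified, or on what is recorded outside the primary count.

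**What to change.** In sections 2.1 and 2.5, and in the matching sentence of the abstract:

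- Define the primary safety result as each patient's worst CTCAE v5.0 grade for any acute skin adverse event in the treated field that is new or worse than the pre-treatment grade, regardless of presumed cause.
- Report the radiation-attributed count beside it, so that a reader sees both numbers and the events that separate them.

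The definition needs a CTCAE grade for the lesion and surrounding skin before the first fraction, if the full protocol does not already take one. Handing the grading to the dermatologist named in section 2.6 (item 13) would not add independence, because that person belongs to the FLASH-RT team: "A FLASH‐RT team consisting of 4 radiation oncologists, 3 radiation physicists, and 1 dermatologist should be established prior to radiotherapy". The remedy is the change of definition.

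The cost is a few lines of text and, at most, one baseline entry; weekly assessment is already planned. The downside is that some tumour-related events will be counted, so the headline rate may be slightly less favourable. The attributed count alongside keeps that visible.
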